### 2.4. Recruitment

Data will be collected in two phases via an online, validated, self-administered questionnaire. Although the data collection strategies may differ across the globe, the target groups are recommended to be approached by governmental, professional, and university networks.

#### 2.4.1. Phase A

A.1. HCWs will be approached by medical and healthcare chambers and/or healthcare professional organizations, and the snowballing technique will be applied;

A.2. Senior adults (≥65) will be approached by the “university of the third age”, by the professional medical association of “young general practitioners”, and by professional organizations for older adults, and the snowballing technique will be applied;

A.3. School teachers will be approached by the networks of educational institutions, while university teachers will be approached via all major universities, and the snowballing technique will be applied;

A.4. Minors (≤18) will be principally approached through their schools, where their parents (or guardians) will be invited to fill in the questionnaire on behalf of their children.

Data collection for the A.1., A.2., A.3., and A.4. population groups will be adjusted according to each participating country’s local setting.

#### 2.4.2. Phase B and C

Volunteers who participate in Phase A and express their interest in self-reporting their long-term side effects will be approached again. The vaccine effectiveness and side effects following booster doses will be investigated in Phase B. Phase C will take place for five consecutive years, starting from 2022.

### 2.5. Timeline

As the local timelines are dependent on the setting of each participating country—including governments’ distribution plans, availability of vaccines, and administrative processes—the proposed timeline is deemed to guide the overall CoVaST progress (Table 1).

### 2.6. Ethics

The study was reviewed and approved by the Ethics Committee of the Faculty of Medicine at Masaryk University on 19 May 2021 (Ref. 26/2021). Ethical clearance will be secured from a designated institutional review board in each participating country before commencement of the study.

Digital informed consent will be obtained from each participant prior to participation. The participants will be allowed to withdraw from the study at any moment without justification, and no data will be saved before the participants submit their answers completely.

### 2.7. Analysis

Descriptive statistics will be performed to check the normality of data distribution, and to present the frequencies and percentages of dependent variables (side effects) and independent variables (demographic data, medical anamneses, and COVID-19-related anamneses). Inferential statistics will be performed to evaluate the potential association of each side effect and the suggested demographic and medical risk factors. All tests will be performed using SPSS 27 (IBM Corp, Armonk, NY, USA), and the significance level cutoff will be set at *p* ≤ 0.05 [32].

## 3. Registration and Dissemination

The study protocol has been registered with the US National Library of Medicine registry (ClinicalTrials.gov, accessed on 9 May 2021), with the identifier NCT04834869 [33]. The ClinicalTrials.gov (accessed on 9 May 2021) record will be regularly updated by the project’s principal investigators, and any deviations from the protocol will be mentioned and justified a priori in the electronic record, and in the manuscript of the final study.

The investigators aim to disseminate the results of the project in peer-reviewed journals on a regular basis. For the results of phase A, the international data for each target group will be published once the data collection is completed. Meanwhile, national data of each participating center will be published as interim results. For the results of phase B, the international data for each target group will be published once the data collection is completed. For the results of phase C, the international data for all target groups will be published on an annual basis once the data collection is completed.

## 4. Discussion

Post-marketing evaluation of vaccines’ safety has typically relied on voluntary reporting of side effects by health care professionals, vaccinated individuals, and caregivers. While there is a surging demand for rigorous pharmacovigilance systems, with active surveillance designs rather than the traditional passive surveillance, a very limited number of high-income countries have managed to develop such systems so far [34].

The United Kingdom (UK) is one of the leading countries in this field, due to its early efforts in developing active surveillance systems for the safety of diphtheria/tetanus/pertussis (DTP) and measles/mumps/rubella (MMR) vaccines since the early 1990s [35]. In terms of COVID-19 vaccines’ safety, the Medicines and Healthcare products Regulatory Agency (MHRA) of the UK has adopted an innovative hybrid system that includes: (a) enhanced passive surveillance through the Yellow Card scheme, where members of the public and healthcare professionals voluntarily report suspected side effects; (b) targeted active monitoring using the Yellow Card scheme; and (c) formal epidemiological studies, such as the OpenSAFELY 17 Collaborative and COVID Symptom Study app [25,36,37].

The results of post-marketing studies may differ to various degrees from the outcomes of phase III trials, where apparently healthy volunteers are usually recruited following strict criteria. Riad et al. found that the overall prevalence of Pfizer–BioNTech ( (Pfizer Inc.: New York City, US) COVID-19 vaccine side effects among recently vaccinated HCWs in the Czech Republic was relatively higher than those reported by the manufacturer [21]. Similarly, the side effects of the Moderna COVID-19 vaccine and the CoronaVac vaccine were more prevalent among HCWs in the US and Turkey, respectively, than the manufacturers’ reports [22,27]. On the other hand, Menni et al. found that the side effects of the Pfizer–BioNTech and Oxford–AstraZeneca COVID-19 vaccines occurred less frequently among a large cohort in the UK than those reported in the phase III trials [25].

The demographic and medical risk factors for side effects’ frequency and intensity are not usually reported by phase III trials, as they are not necessarily outcomes of interest during this stage. Therefore, post-marketing studies are in an ideal position to confirm or refute suggested risk factors, using large datasets of self-reported outcomes. For example, all post-marketing studies of mRNA vaccines found that the frequency of side effects following the second dose is higher than after the first dose [21,23,24,25]. The phase III trials displayed the same pattern; therefore, the post-marketing studies only came to confirm this preliminary finding [38,39]. Female gender was consistently associated with an increased risk of side effects following different types of COVID-19 vaccines; interestingly, the gender-based differences were reported by manufacturers [21,22,23,25,28].

As more COVID-19 vaccines are currently in the pipeline of clinical trials and authorization, readily available instruments for active surveillance will be much needed in order to shorten the time period of post-marketing investigation by academic institutions. Moreover, the prospective booster doses’ safety should be evaluated in relatively shorter periods of time, in order to relieve our weakened healthcare systems. Therefore, the CoVaST project aims to provide an international infrastructure for active surveillance of booster doses’ side effects and the long-term safety and effectiveness of COVID-19 vaccines.

### Strengths and Limitations

To the best of the authors’ knowledge, this is the first multinational study aiming to monitor the safety of various COVID-19 vaccines, especially following booster doses. Another strong point of this study is its unified evaluation instrument, target groups, and methods, which will be used in all participating countries, and should maximize the results’ internal validity. Recruiting HCWs is intended to limit the reporting bias that is naturally predicted in this survey-based study, due to the fact that HCWs retain high levels of health literacy and scientific interest. This study is one of the early-registered studies that are concerned with the long-term safety of COVID-19 vaccines, and their effectiveness.

In general, this study is limited by the heterogeneous time span between vaccination and survey commencement across the participating countries; therefore, subgroup analysis according to the time span will be carried out during data analysis. One more limitation is recall bias, as in various countries, vaccination covered the majority of population who intended to be vaccinated. Due to the recruitment of participants who received the vaccine in the first half of 2021, there is a possibility of recall bias when filling out the questionnaire. Since COVID vaccination is a hot topic worldwide, we assume that participants could remember all experienced side effects well.

## 5. Conclusions

The side effects of COVID-19 vaccines require active surveillance in the post-authorization phase, as the side effects can potentially impact decisions regarding vaccination. CoVaST, as a multi-national study, aims to evaluate the short-term and long-term side effects and effectiveness of various COVID-19 vaccines.

## Figures and Tables

**Figure 1 ijerph-18-07859-f001:**
[figure not shown]
Sample size of healthcare workers (HCWs) in the Czech Republic—Epi-Info ^TM^ version 7.2.4. Population size: Total number of healthcare workers in the Czech Republic in 2017 [30]. Expected frequency: The overall prevalence of side effects following COVID-19 vaccines ranged between 62% and 93%; therefore, 60% was assumed as a threshold. Acceptable margin of error: The permissible level for all CoVaST groups will be 5%. Design effect: One—per the recommendation of the CDC for simple sampling [29]. Clusters: One—per the recommendation of the CDC for simple sampling [29]. The pragmatic sample size is 368–635 (CI 95%–99%).

**Table 1 ijerph-18-07859-t001:** The projected timeline of the COVID-19 vaccines safety tracking (CoVaST) study.

Phase	Stage	Population	Schedule
Phase A	Stage A.1.	HCWs	May–August 2021
	Stage A.2.	SAs	June–December 2021
	Stage A.3.	TAs	June–December 2021
	Stage A.4.	MIs	June–December 2021
Phase B	Stage B.1.	HCWs	October 2021–February 2021
	Stage B.2.	SAs	November 2021–April 2022
	Stage B.3.	TAs	November 2021–April 2022
	Stage B.4.	MIs	November 2021–April 2022
Stage C	Stage C.1.	HCWs, SAs, TAs, MIs	January–December 2022
	Stage C.2.	HCWs, SAs, TAs, MIs	January–December 2023
	Stage C.3.	HCWs, SAs, TAs, MIs	January–December 2024
	Stage C.4.	HCWs, SAs, TAs, MIs	January–December 2025
	Stage C.5.	HCWs, SAs, TAs, MIs	January–December 2026

HCWs = Healthcare Workers; SAs = Senior Adults; TAs = Teachers and Academics; MIs = Minors.

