#### 2.2.3. Sample Size

The pragmatic sample size for each target group in each country will be calculated using Epi Info ^TM^ version 7.2.4 (CDC, Atlanta, GA, USA. 2020). The formula of population survey studies will be used to achieve a 5% margin of error and a 95–99% confidence level [29]. The expected frequency (outcome probability) is assumed to be 60%, as the prevalence of side effects following COVID-19 vaccines ranged between 62% and 93% in our previous studies [21,22] (Figure 1).

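### Figure 1 sizes every group as a simple sample (design effect 1), but recruitment is by snowballing and through schools, so the 5% margin at 95–99% confidence is not assured

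*Protocol article*

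**What the plan says.** Section 2.2.3 sizes each target group in each country: "The formula of population survey studies will be used to achieve a 5% margin of error and a 95–99% confidence level". In the same section, "The expected frequency (outcome probability) is assumed to be 60" per cent, set just under the 62–93% seen in the authors' previous studies.

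Figure 1 works the example of Czech healthcare workers. Two of its inputs carry the same reason: "Design effect: One—per the recommendation of the CDC for simple sampling" and "Clusters: One—per the recommendation of the CDC for simple sampling". The result is 368 at 95% confidence and 635 at 99%. The legend extends the margin beyond the example: "The permissible level for all CoVaST groups will be 5" per cent.

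Section 2.4.1 (Phase A) describes how people are found. Healthcare workers come through chambers and professional organisations, senior adults through the university of the third age, general practitioners and older adults' organisations, and teachers and academics through educational institutions and universities. For each of these three groups the text adds "and the snowballing technique will be applied". Minors "will be principally approached through their schools"; snowballing is not mentioned for them.

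Strengths and Limitations names the varying time since vaccination and recall bias. It does not mention the sampling method.

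**The concern.** The reason given for a design effect of 1 is that the sample is simple, and none of the four groups is sampled that way. People who share a referrer, an employer or a school are likely to share vaccine brand, vaccination period and reporting habits. Their answers are then positively correlated, and a prevalence estimate has more variance than the binomial formula allows.

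The first primary objective is to estimate the prevalence of side effects, and the 5% margin is the only precision the article promises for it. National results are to be published as interim results, so an overstated precision would be repeated country by country. The figure 368 also reappears in section 2.2 as the threshold for additional Phase B recruitment.

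**Working it through.** **Inputs.** Prevalence p = 0.60 and margin d = 0.05 (section 2.2.3); design effect (DEFF) 1 and one cluster (Figure 1); two-sided z = 1.960 for 95% and 2.576 for 99%. For the finite-population correction Figure 1 uses "Population size: Total number of healthcare workers in the Czech Republic in 2017"; the number itself is not in the text at hand, so N = 200,000 to 250,000 is assumed.

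**Reproducing the plan's figure.**

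- Without the correction, n = z²p(1−p)/d². At 95%: 1.960² × 0.24 / 0.0025 = 368.8. At 99%: 2.576² × 0.24 / 0.0025 = 637.0.
- With the correction, n = N·p(1−p) / [(d²/z²)(N−1) + p(1−p)]. This gives 368.1 to 368.2 at 95% and 634.9 to 635.3 at 99%.

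Both stated figures are reproduced with DEFF = 1.

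**Slack at the plan's own inputs.** Half-width = z·√(DEFF × 0.24 / n). With DEFF = 1 it is 5.01 points for n = 368 at 95% and 5.01 points for n = 635 at 99%. Nothing is left over for clustering.

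**Effect of a design effect above 1.** The documents give no intra-cluster correlation and no cluster size, so the range below is an assumption. The half-width is the same for both pairings because each n was solved for the same margin.

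| Assumed DEFF | Half-width: n = 368 at 95%, or n = 635 at 99% | Confidence of a ±5-point interval, n = 368 | Same, n = 635 | n to restore 5 points (368 or 635 × DEFF) |
|---|---|---|---|---|
| 1 | 5.0 points | 95% | 99% | 368 / 635 |
| 1.5 | 6.1 points | 89% | 96% | 552 / 953 |
| 2 | 7.1 points | 83% | 93% | 736 / 1,270 |
| 3 | 8.7 points | 74% | 86% | 1,104 / 1,905 |

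For orientation, DEFF = 1 + (m − 1) × ICC for clusters of m respondents. An assumed m = 20 and ICC = 0.05 give 1 + 19 × 0.05 = 1.95; m = 10 and ICC = 0.01 give 1.09.

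**Where there is room.** The largest DEFF that keeps 5 points is n·d² / [z²p(1−p)].

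- n = 635 read at 95%, p = 0.60: 635 × 0.0025 / (3.842 × 0.24) = 1.72.
- n = 368 at 95%, p = 0.62: 1.02.
- n = 368 at 95%, p = 0.775 (the middle of 62–93%): 0.92 / (3.842 × 0.1744) = 1.37.
- n = 368 at 95%, p = 0.93: 0.92 / (3.842 × 0.0651) = 3.68.

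**The case against.** The strongest reply has four parts.

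1. **The range goes up to 635.** A country that recruits 635 and reports at 95% confidence has a half-width of 3.8 points at DEFF 1 and 4.7 at DEFF 1.5, and stays within 5 points up to about 1.72. This stands. What fails at 635 under moderate clustering is the 99% level, not a 95% margin of 5 points.

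2. **60% is a cautious input.** Prevalence inside the cited 62–93% range adds room: almost none at 62%, but up to DEFF 1.37 at 77.5% and about 3.7 at 93% with n = 368. This also stands. The room depends on how the prevalence turns out, so it is not something the plan can promise in advance.

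3. **The size of the shortfall is assumed.** No design effect, cluster size or correlation is given. That is correct, and it is why only a range is shown. It does not restore the stated reason for choosing 1.

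4. **The article calls the size pragmatic, and an analysis plan may handle clustering.** Both are fair. The point here is not a missing variance method. It is an input, with its justification, that the article itself fixes and that its own recruitment section contradicts.

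A reader might go further and infer that every confidence interval and risk-factor test will be too narrow. The documents do not support that. The DEFF formula used here is for a proportion. A comparison made within clusters, such as by sex, age or comorbidity, need not lose precision and may gain it. Section 2.7 also fixes no variance estimator. A reader might likewise infer that a precision claim for results pooled across countries is broken, but the article makes none: section 2.2.3 sizes each group within each country.

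**Conclusion.** The concern holds in a limited form. The arithmetic behind 368 and 635 is right, but it belongs to a simple random sample, and section 2.4.1 describes something else for all four groups. With 60% prevalence and no slack, the 5% margin at the paired confidence level is not assured: about 6.1, 7.1 or 8.7 points if the design effect is 1.5, 2 or 3.

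To say outright that the margin will be missed would be too strong. That depends on a design effect the documents do not give, on whether a country recruits nearer 368 or 635, on the confidence level reported and on the true prevalence.

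A further limit holds at any sample size. Snowballing leaves selection probabilities unknown, so a margin of error describes sampling variation only. A larger n or a design effect would not cover selection bias.

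**What to change.** - **Section 2.2.3 and Figure 1.** Remove the simple-sampling reason for design effect 1 and one cluster. Describe 368–635 as a nominal or pragmatic minimum and show the margin over a stated design-effect range. Possible wording: *The sizes 368 and 635 would give a 5-point margin at 95% and 99% confidence, respectively, for a simple random sample with 60% prevalence. Recruitment is not a probability sample; with a design effect of 1.5 to 3 the margin would be about 6 to 9 points. These margins cover sampling error only.*
- **Strengths and Limitations.** List non-probability (snowball) sampling beside the limitations already given.
- **Data collection and analysis, only where there are many identifiable clusters.** For minors, record a coded school identifier and use cluster-robust intervals for prevalence. This is not advised across a handful of recruitment-channel types: robust variance is unreliable with few clusters, and a channel field does not identify referral chains.

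**Cost.** Wording, and one coded field for minors, which is best captured at the time because it may not be recoverable later. No extra participants are needed. The price is a less favourable stated precision. The changes make the claim honest; they do not restore 5 points, which would take the larger numbers in the table.

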## Data Availability

The data that support the findings of this study are available from the corresponding author upon reasonable request.
